## Abstract

**Background:**

Connective tissue links the skeletal muscles, creating a body-wide network of continuity. A recent in-vivo experiment demonstrated that passive elongation of the calf caused a caudal displacement of the semimembranosus muscle, indicating force transmission across the dorsal knee joint. However, it remains unclear as to whether this observation is dependent on the joint angle. If force would not be transmitted at flexed knees, this would reduce the number of postures and movements where force transmission is of relevance. Our trial, therefore, aims to investigate the influence of passive calf stretching with the knee in extended and flexed position on dorsal thigh soft tissue displacement.

**Methods:**

Participants are positioned prone on an isokinetic dynamometer. The device performs three repetitions of moving the ankle passively (5°/s) between plantar flexion and maximum dorsiflexion. With a washout-period of 24 hours, this procedure is performed twice in randomised order, once with the knee extended (0°) and once with the knee flexed (60°). Two high-resolution ultrasound devices will be used to visualize the soft tissue of the calf and dorsal thigh during the manoeuvre. Maximal horizontal displacement of the soft tissue [mm] during ankle movement will be quantified as a surrogate of force transmission, using a frame-by-frame cross-correlation analysis of the obtained US videos.

**Discussion:**

Understanding myofascial force transmission under in-vivo conditions is a pre-requisite for the development of exercise interventions specifically targeting the fascial connective tissue. Our study may thus provide health and fitness professional with the anatomical and functional basis for program design.

**Trial registration:**

The study is registered at the German Clinical Trials Register (TRN: DRKS00024420), registered 8 Februar 2021, https://www.drks.de/drks_web/navigate.do?navigationId=trial.HTML&TRIAL_ID=DRKS00024420.

## Introduction

It is a long-held belief that fascia, the collagenous connective tissue surrounding the skeletal muscle, represents a passive packing organ with limited significance for the locomotor system [1]. However, recent research has not only revealed its contribution to proprioception and pain [2–4]. Beyond providing sensory input [2–4], fascial tissue has been demonstrated to connect both, parallelly [5] (e.g. gastrocnemius and soleus) and serially [6, 7] (e.g. gastrocnemius and Hamstrings) arranged muscles. Following this paradigm, Wilke et al. [6] found strong evidence for the existence of a posterior myofascial chain, consisting of the plantar fascia, Achilles tendon, gastrocnemius muscle and fascia, Hamstring muscles and fasciae, sacrotuberous ligament, lumbar fascia, and erector spinae muscle and fascia. Interestingly, biomechanical experiments in cadavers showed that significant forces may be transmitted via the described tissue continuities [8, 9]. Yet, due to fixation of cadavers using solutions such as formaldehyde, the findings cannot be readily interpolated to in-vivo conditions.

Only few studies have investigated myofascial chains and their mechanical relevance in the living organism. Most of these found non-local improvements of range of motion (ROM) after stretching or self-massage applied at distant, structurally connected body locations [10–12]. However, as ROM represents a functional outcome, these observations cannot be considered as valid proofs of force transmission. With a pioneering experiment, Crus-Montecinos et al. [13] provided initial direct evidence for a mechanical interaction of serially connected muscles, revealing by means of high-resolution ultrasound imaging that an anterior pelvic tilt is associated with an cranial displacement of the deep fascia of the gastrocnemius. Hereafter, Wilke et al. [14] first investigated myofascial force transmission in the opposite (caudal to cranial) direction. In an exploratory trial, they examined the impact of ankle motion on soft tissue displacement of the dorsal thigh. In a prone position and with the knee extended, the ankle of eleven healthy individuals was passively moved between plantar flexion and dorsal extension by an isokinetic dynamometer. Simultaneous ultrasound recordings revealed a caudal displacement of the semimembranosus muscle. Despite these intriguing findings, the trial of Wilke et al. [15] had a small sample size and no control condition.

Movements like walking, squatting or jumping require a change and interaction between flexion and extension, especially in the ankle and knee joints. From a theoretical point of view, to transmit force from the calf muscles to the posterior thigh, the tissue connection between the gastrocnemius and the Hamstrings needs to be stiffened. Anatomically, the gastrocnemius attaches to the medial and lateral epicondyles of the femur. In view of the resulting biarticularity, extension of the knee leads to a higher stretch of the gastrocnemius when compared to flexion of the knee [16]. As the gastrocnemius and its fascial connection to the Hamstrings are lengthened and stiffened when approaching knee extension while becoming slack when approaching knee flexion, we expect a higher degree of force transmission at knee extension. So far, it is unknown as to whether myofascial force transmission is dependent on the joint position. Knowledge about this factor is, however, crucial: if no forces would be transmitted at flexed knees, this would mean that the number of postures, movements and situations where force transmission is of relevance, is reduced. As a consequence, the planned study aims to investigate the influence of passive calf stretching with the gastrocnemius in fully elongated (knee extended) and slack (knee flexed) position on dorsal thigh soft tissue displacement.

We hypothesize that (1) passive ankle motion at knee extension causes caudal displacements of the Hamstring muscles while little or no displacement can be seen at knee flexion and (2) the degree of Hamstring muscle displacement is dependent on ankle movement.

## Materials and methods

### Study design

The trial adopts a randomized crossover design (Fig 1). All enrolled participants will undergo two examinations, which are separated by a washout period of 24 hours: Displacement of the semimembranosus and its fascia upon ankle joint motion will be examined with the knee in (1) extended and (2) flexed position. To exclude possible influences of circadian rhythm, the examinations will be performed at the same daytime and in the same room.

**Fig 1 pone.0276240.g001:**
[figure not shown]
Flow of participants.

### Sample

Healthy active individuals, both males and females, aged between 18 and 40 years will be enrolled. Exclusion criteria are defined as severe orthopedic, cardiovascular, neurological, endocrine and psychiatric diseases, acute inflammation, intake of drugs that modify pain perception and proprioception, delayed onset muscle soreness, pregnancy or nursing period and history of surgery in the lower limb. Flyer, poster advertising, as well as personal addressing will be used for recruitment.

### Ethics approval and consent to participate

The trial will be conducted according to the Guidelines of Good Clinical Practice and according to the Declaration of Helsinki including its recent modification of Fortaleza. The local ethics committee of Goethe University Frankfurt (2020-71G) has obtained ethical approval on 23^rd^ December 2020. All participants will provide written informed consent. The collection, transfer, storage and analysis of personal data will be performed in accordance with applicable law.

### Patient and public involvement

Patients and Public were not involved in the design and conduct of the study, as well as in the choice of outcome measures and recruitment.

### Experimental approach

Participants are positioned prone on an isokinetic dynamometer (IsoMed 2000, D. & R. Fersti GmbH, Hemau, Germany). The ankle (tested leg chosen randomly) will be moved passively from plantar flexion to the maximal achievable dorsal extension using the continuous passive motion function, which constantly moves the joint through the set range of motion. Based on previous studies, after a warm-up of three plantar flexion-extension cycles [8], three repetitions are performed at an angular velocity of 5°/s [13, 15]. Secondary movement of the knee and the pelvis is minimized by means of velcro straps. The participants are instructed to avoid any voluntary muscle activity. To verify muscle inactivity, surface electromyography (sEMG) (BioNomadix EMG2, Biopac Systems Inc., Goleta, CA, United States) of the semimembranosus and gastrocnemius medialis will be applied. Additionally, sEMG will be used to provide the participants with live biofeedback. To reduce impedance between electrodes and the skin, the area of application will be shaved and cleaned. According to the SENIAM guidelines [17], electrodes will be placed on the most prominent bulge of the gastrocnemius medialis and semimembranosus muscles. In order to identify the correct locations for electrode placement, ultrasound (US) will be used. All electrodes will be placed with an inter-electrode distance of 2 cm and following the longitudinal axis of the muscle [17]. All included individuals, in randomized order, undergo the above described assessment procedure twice. In one session, the knee is fixed in extension (0° knee angle) while in the other condition, the knee is fixed in 60° flexion. This angle was chosen, because the gastrocnemius has been shown to be slack in this position [18]. A schematic depiction of the experimental approach is shown in Fig 2.

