### Data processing and outcome

The maximal horizontal displacement [mm] of the semimembranosus will be quantified using cross-correlation analysis of the videos visualizing the dorsal thigh. Briefly, within pre-defined regions of interest (ROI), the used MATLAB (The MathWorks, Inc., Natick, MA, United States) based algorithm [19] determines the correlation coefficient between the pixel gray levels of successive frames (Fig 3). The algorithm of Dilley et al. [19] has been shown to represent a reliable method to quantify tissue displacement (ICC .7 to .99). High precision (error of 0.1 to 0.3 mm for displacements between 1 and 3 mm) of the algorithm has been demonstrated [19]. In the planned trial, six equidistant ROIs will be used. Excellent reliability of this approach has been demonstrated before [8, 15].

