**Fig 3 pone.0276240.g003:**
[figure not shown]
Exemplary visualization of US cross-correlation analysis. Here, five ROIs (red rectangles) have been positioned at rest (left image): three within the fascia and one in each, the subcutaneous tissue (SCT) and the muscle ROIs. The small yellow squares within the ROIs represent the center of the non-moving ROIs. Upon movement (right image), pixel displacement relative to the center of the non-moving ROIs are tracked (yellow line in right picture). The end of the line indicates the maximal displacement, computed by the software algorithm.

Besides measuring semimembranosus displacement, we will examine the displacement [mm] of the gastrocnemius muscle during the ankle movement. Using the same cross-correlation analysis as described before. In the videos of the calf, four ROIs will be placed in the lower aponeurosis of the gastrocnemius muscle.

The recorded US data and the ROM measurements of the dynamometer, as well as the EMG data will be synchronized using a common interface (AcqKnowledge, Biopac Systems Inc., Goleta, CA, United States). To detect unwanted muscle activity, the implemented function of the interface to locate muscle activity will be used. First, the algorithm determines the mean and standard deviation of the EMG signal under resting conditions over a 0.25 s period. Based on the algorithm of Hodges and Bui [20], a filtered average rectified value (AVR) will be computed. The variance with regard to the noise will be extracted dividing the difference between the ARV and the mean by the standard deviation. For the resulting signal, the median is calculated for the entire waveform and any activity exceeding this median for at least 0.1 s will be considered as muscle activity [20] and will be excluded from the analysis.

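### The H1 test compares maximal displacement at two knee positions without matching ankle excursion, so a null or reversed result would be ambiguous

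*Protocol article*

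**What the plan says.** Experimental approach describes the movement: "The ankle (tested leg chosen randomly) will be moved passively from plantar flexion to the maximal achievable dorsal extension". The dynamometer runs in continuous passive motion mode, "which constantly moves the joint through the set range of motion". On repetition it says: "All included individuals, in randomized order, undergo the above described assessment procedure twice", with the knee at 0° in one session and at 60° in the other. The Abstract likewise ends the movement at maximum dorsiflexion. No section states an end angle, a torque limit or a range shared by the two knee positions.

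The Introduction says that "extension of the knee leads to a higher stretch of the gastrocnemius when compared to flexion of the knee". Experimental approach chose 60° because the gastrocnemius is slack there. Hypothesis 2 is that "the degree of Hamstring muscle displacement is dependent on ankle movement".

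Under Data processing and outcome: "The maximal horizontal displacement [mm] of the semimembranosus will be quantified", in millimetres and not at a stated ankle angle. Statistics averages the three repetitions and compares the knee positions by a paired t test, or a Wilcoxon test if the data are not normal. Ankle angle is averaged per condition too, but enters only the regression for hypothesis 2. The Abstract treats displacement as a surrogate of force transmission.

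**The concern.** If the ankle travels further in one condition, and displacement grows with ankle travel, the paired difference has two sources: the knee position under study and the extra travel. Randomising the order of sessions does not separate them, because the extra travel comes with the knee position itself.

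The stake is the question the trial poses in its Introduction: whether transmission depends on joint position, and whether it matters at flexed knees. A null or reversed result could mean that transmission is similar at both positions, or that weaker transmission at the flexed knee was offset by a longer ankle movement. The planned Cohen's d, which Statistics uses to judge clinical relevance, would carry the same mixture.

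**Working it through.** **The plan's own figures.** The article gives no excursion data, so there is no stated excursion to reproduce. The sample size for hypothesis 1 (n = 29; α = .05, power .8, d = .5, 5% dropout) reproduces as a one-sided paired t test: 27, and 27/0.95 = 28.4, rounded up to 29. A two-sided test needs 34, or 36 after dropout. Planned enrolment of 56 covers both, and this point does not dispute it.

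**Chain of reasoning from the text.**
1. The end point is the maximal achievable dorsiflexion, in a procedure done at 0° and again at 60° (Experimental approach; Abstract).
2. The gastrocnemius is stretched at 0° and slack at 60° (Introduction; Experimental approach), so more dorsiflexion is likely at 60°.
3. Displacement depends on ankle movement (hypothesis 2).
4. The hypothesis 1 outcome and test contain no ankle-angle term (Data processing and outcome; Statistics).

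**Size, on assumed inputs.** Assume 0.05 mm of displacement per degree and 40° of excursion with the knee extended, δ = 5° or 10° more with the knee flexed, and flexed transmission per degree equal to a fraction f of extended. None of these values is in the article.

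- Difference at equal excursion: 0.05 × 40 × (1 − f) = 2.00 × (1 − f)
- Difference at each condition's own maximum: 0.05 × 40 − f × 0.05 × (40 + δ)

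| f | Equal excursion | Own maximum, δ = 5° | Own maximum, δ = 10° |
|---|---|---|---|
| 0.2 | 1.60 mm | 2.00 − 0.45 = 1.55 mm | 2.00 − 0.50 = 1.50 mm |
| 0.5 | 1.00 mm | 2.00 − 1.125 = 0.875 mm | 2.00 − 1.25 = 0.75 mm |
| 0.8 | 0.40 mm | 2.00 − 1.80 = 0.20 mm | 2.00 − 2.00 = 0.00 mm |
| 1.0 | 0.00 mm | 2.00 − 2.25 = −0.25 mm | 2.00 − 2.50 = −0.50 mm |

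As a share of extended-knee displacement, the loss is f × (q − 1), where q is the excursion ratio flexed/extended. It does not depend on the 0.05 mm figure and is zero when f = 0. The sign reverses once f exceeds 1/q: 40/45 = 0.89 for δ = 5° and 40/50 = 0.80 for δ = 10°.

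**Effect on power, also on assumed shifts.** With 53 participants (56 less about 5%) and a two-sided test at .05, a true standardised difference of 0.5 gives 95% power. A shift of 0.1, 0.2 or 0.3 against it lowers this to 82%, 57% or 30%.

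**The case against.** A reader might infer that the protocol prescribes separate maxima and so guarantees unequal excursions. It does not. The phrase about the set range leaves open whether the range is fixed once per participant or once per session, and the full protocol may settle it. That excursions differ follows from the stated anatomy, not from any figure. Both steps are inferences, though the natural ones.

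A reader might also infer that the bias could manufacture support for hypothesis 1. On the protocol's anatomy it runs the other way. If flexed-knee transmission is near zero, as hypothesis 1 expects, the distortion is negligible. The large distortions arise only where transmission is similar at both positions, so that hypothesis 1 is largely or wholly false. The model also assumes constant displacement per degree, while the protocol describes tissue passing from slack to stiff.

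Displacement over each posture's full range is moreover a defensible quantity. It addresses whether any transmission occurs at flexed knees, and matching discards the end of the flexed-knee range, where such transmission may be most likely to appear. This stands, and is a reason to keep the own-maximum result and not replace it.

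Finally, ankle angle is recorded in both conditions, so an ambiguous result could be examined afterwards. That is true, but an excursion adjustment chosen after seeing a null or reversed result would carry less weight than one fixed beforehand.

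**Conclusion.** The point holds as a worthwhile and cheap improvement. It does not show that the hypothesis 1 test is unusable. As written, the test does not separate knee position from ankle excursion. If excursion is larger with the knee flexed, a result favouring extension keeps its direction but understates the matched-range difference in millimetres, and d is distorted with it. A null or reversed result would be ambiguous.

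On the assumed inputs, the loss is 0.05-0.10 mm of 1.60 mm at 20% relative transmission and 0.20-0.40 mm of 0.40 mm at 80%. At equal transmission there is a spurious −0.25 to −0.50 mm. These sizes rest on assumed slope, excursion and linearity. The direction rests on the protocol's anatomy and on the maximum being sought at each knee position.

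**What to change.** State whether the ankle range is set once per participant or separately at each knee position. If separately, pre-specify for hypothesis 1 a paired comparison of semimembranosus displacement over an ankle range common to both conditions within each participant. The range has a common plantar-flexion start, and its upper limit is the smaller of that participant's two maximal dorsiflexion angles. The data for this are already planned: "The recorded US data and the ROM measurements of the dynamometer, as well as the EMG data will be synchronized using a common interface".

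Report this alongside displacement at each condition's own maximum, and report ankle excursion by condition. Base any statement that transmission as such depends on knee position on the matched-range comparison.

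The cost is some analysis wording and a little more data extraction, with no new measurement. The matched analysis leaves out the end of the larger range, probably the flexed-knee one, which is why the own-maximum result is kept beside it.

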**Fig 2 pone.0276240.g002:**
[figure not shown]
Experimental approach. All participants will undergo two testing conditions. In randomized order, in prone position, the ankle will be moved between plantar flexion and dorsal extension by use of a dynamometer (arrows) with the knee in extended (A) and flexed (B) position. In both conditions, ultrasound recordings of the calf and dorsal thigh will be made to estimate tissue displacement induced by the ankle motion.

To visualize tissue displacement upon ankle movement, two high-resolution ultrasound devices (Siemens Acuson X300 PREMIUM EDITION, Siemens Medical Solutions USA, Inc., Mountain View, CA and Siemens Acuson Redwood, Siemens Healthcare GmbH, Erlangen, Germany) will be used. Video recordings are made using linear array transducers (VF10-5 linear array, 5,0–10,0 MHz, Siemens Medical Solutions USA, Inc., Mountain View, CA and 10L4 linear array, 3,3–11,4 MHz, Siemens Healthcare GmbH, Erlangen, Germany) positioned over (1) the gastrocnemius and (2) the semimembranosus muscle.

### Data processing and outcome

The maximal horizontal displacement [mm] of the semimembranosus will be quantified using cross-correlation analysis of the videos visualizing the dorsal thigh. Briefly, within pre-defined regions of interest (ROI), the used MATLAB (The MathWorks, Inc., Natick, MA, United States) based algorithm [19] determines the correlation coefficient between the pixel gray levels of successive frames (Fig 3). The algorithm of Dilley et al. [19] has been shown to represent a reliable method to quantify tissue displacement (ICC .7 to .99). High precision (error of 0.1 to 0.3 mm for displacements between 1 and 3 mm) of the algorithm has been demonstrated [19]. In the planned trial, six equidistant ROIs will be used. Excellent reliability of this approach has been demonstrated before [8, 15].

**Fig 3 pone.0276240.g003:**
[figure not shown]
Exemplary visualization of US cross-correlation analysis. Here, five ROIs (red rectangles) have been positioned at rest (left image): three within the fascia and one in each, the subcutaneous tissue (SCT) and the muscle ROIs. The small yellow squares within the ROIs represent the center of the non-moving ROIs. Upon movement (right image), pixel displacement relative to the center of the non-moving ROIs are tracked (yellow line in right picture). The end of the line indicates the maximal displacement, computed by the software algorithm.

Besides measuring semimembranosus displacement, we will examine the displacement [mm] of the gastrocnemius muscle during the ankle movement. Using the same cross-correlation analysis as described before. In the videos of the calf, four ROIs will be placed in the lower aponeurosis of the gastrocnemius muscle.

The recorded US data and the ROM measurements of the dynamometer, as well as the EMG data will be synchronized using a common interface (AcqKnowledge, Biopac Systems Inc., Goleta, CA, United States). To detect unwanted muscle activity, the implemented function of the interface to locate muscle activity will be used. First, the algorithm determines the mean and standard deviation of the EMG signal under resting conditions over a 0.25 s period. Based on the algorithm of Hodges and Bui [20], a filtered average rectified value (AVR) will be computed. The variance with regard to the noise will be extracted dividing the difference between the ARV and the mean by the standard deviation. For the resulting signal, the median is calculated for the entire waveform and any activity exceeding this median for at least 0.1 s will be considered as muscle activity [20] and will be excluded from the analysis.

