## Discussion

The relevance of the extramuscular connective tissue for locomotor mechanics represents one of the main focuses of fascia research [23]. However, evidence on force transmission, hitherto, has mostly been derived from cadaver studies and experiments using functional outcomes (i.e. ROM, [8, 10–12]). As a consequence, it is unclear if observed remote exercise effects (e.g. flexibility increases) are due to mechanical interactions or neural adaptations such as a systemic reduction of stretch tolerance [24]. Against this background, the planned trial will help to more conclusively delineate the contribution of tissue continuity. Its main purpose is to investigate the influence of passive calf stretching with the knee extended or flexed on dorsal thigh soft tissue displacement.

The results of the planned trial, will also provide more definitive practical insights into how stretching transmits force to adjacent structures by visualizing remote tissue behavior as a function of joint angle. With regard to the dorsal knee, it will particularly allow the identification of movements and situations where myofascial force transmission may play a role or not. From a more general point of view, therapists and exercise professionals count among the groups that may benefit from our findings. Limitations in ROM have been associated with several musculoskeletal pathologies such as groin pain [25] or low back pain [26]. Traditionally, related active treatments have been based on the application of local flexibility treatments. However, as a couple of studies have demonstrated the existence of non-local exercise effects following clinical treatments based on myofascial chain concepts [10–13], our study may provide further arguments for their use.

Our study has several methodological strengths. For instance, first, it is based on very similar pilot works and a robust sample size calculation, allowing sufficient power to detect clinically relevant force transmission effects. Second, it uses established procedures and valid devices (e.g. isokinetic dynamometer) to control for potentially relevant confounders such as involuntary muscle activation (EMG measurements) or probe displacement (ultrasound-based movement analysis system).

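### The EMG exclusion rule takes its threshold from the median of the recording itself, so the resting baseline has no effect and the offline step can flag rest or miss sustained contraction

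*Protocol article*

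**What the plan says.** The rule stands in the protocol article under Data processing and outcome, in the text after Fig 3. It has four steps.

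1. Baseline: "the algorithm determines the mean and standard deviation of the EMG signal under resting conditions over a 0.25 s period".
2. Normalisation of the filtered average rectified value (ARV): "dividing the difference between the ARV and the mean by the standard deviation".
3. Threshold: "For the resulting signal, the median is calculated for the entire waveform".
4. Decision: "any activity exceeding this median for at least 0.1 s will be considered as muscle activity", and such activity "will be excluded from the analysis".

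The article gives no multiple of the median and no SD offset. It does not state the filter cut-off, or whether a flag removes samples, a repetition or a recording.

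Under Experimental approach the muscle is meant to be quiet throughout: "The participants are instructed to avoid any voluntary muscle activity". The same section says that sEMG also serves as live biofeedback. Under Statistics, displacement is averaged over three repetitions per condition and muscle. The Discussion names EMG among the means of controlling confounding by involuntary activation.

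**The concern.** A detection threshold should separate activity from rest. The median of a recording cannot do this by itself, because half of the samples lie above it whatever the muscle does. Only the 0.1 s duration condition then decides what is flagged, and how well that works depends on the smoothing.

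Two errors can follow. In a relaxed participant, smoothed noise can stay above the median for 0.1 s and be removed as contraction. In a participant who contracts for more than half of the recording, the median rises to the contracted level and part or most of the contraction passes as rest. The trial wants to attribute thigh displacement to passive transmission, and each condition mean rests on only three repetitions. It therefore matters which data this step removes and which it keeps.

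**Working it through.** The article states no error rate for the rule, so there is no figure to reproduce. The check has an exact part and a simulated part.

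**Exact part (no assumptions).** Let m and s > 0 be the resting mean and SD, and z = (ARV − m)/s. Then median(z) = (median(ARV) − m)/s, so z > median(z) exactly when ARV > median(ARV). Both m and s cancel.

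Since half of the samples exceed the median, the share of contracted time that can be flagged has a ceiling under any smoothing:

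- contraction over 60% of the record: at most 0.5/0.6 = 83.3%
- over 80%: at most 0.5/0.8 = 62.5%
- over 90%: at most 0.5/0.9 = 55.6%
- over 100%: at most 50%, the same ceiling as at rest.

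**Simulated part.** Inputs from the article: threshold at the whole-waveform median, minimum duration 0.1 s, baseline 0.25 s. Assumptions, because the article does not give them: band-limited noise as resting EMG, a contraction at 5 times the resting amplitude, and low-pass smoothing of the rectified signal at several cut-offs. The ranges cover single-pass (lower values) and zero-phase (higher values) filtering.

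| Low-pass cut-off | Fully relaxed record: time flagged | 5-fold contraction over 90% of record: contracted time flagged |
|---|---|---|
| 2 Hz | 47–50% | 53–55% |
| 10 Hz | 16–28% | 23–34% |
| 50 Hz | about 0% | 0–0.5% |

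In the same contracted records, a threshold at resting mean + 3 SD marks over 99% of the contracted time.

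A second simulation used 36 s records, 100 per setting, and seven smoothers (low-pass 3, 6, 10 and 50 Hz; moving average 30, 100 and 250 ms).

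- **Rest only:** at least one flag in 100% of records for six smoothers and in 32% for low-pass 50 Hz. Time flagged was 0.1% to 48.5%. At 6 Hz, record lengths of 12, 36 and 72 s all gave about 41%.
- **Contraction over the whole record:** 0.2% to 48.5% of time flagged, practically the same as at rest.
- **Contraction over 10% of the record:** all of it flagged. Of the resting remainder, 21.5% to 42.7% was also flagged at low-pass 3–10 Hz and moving average 100–250 ms, 1.5% at moving average 30 ms and 0.1% at low-pass 50 Hz.

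**Rest-based rule.** False flags of relaxed records with mean + 3 SD depend on baseline length and smoothing. In single-pass runs, at 5 Hz, 29–38% of records were flagged with a 0.25 s baseline and 1.5% with a 5 s baseline. At 10 Hz and above, a 5 s baseline gave about 0%. At 2 Hz, even a 5 s baseline still flagged 22–38%.

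**The case against.** Five points can fairly be made for the plan.

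- **Brief contractions are found.** With light smoothing they are found with almost no false flags. This stands: it would be wrong to say that the rule detects nothing.
- **Other safeguards exist.** Participants are told to stay relaxed and receive live biofeedback, and neither depends on the median. This stands. A reader might infer that involuntary activation is not controlled at all, but the article does not support that. Biofeedback also makes long contractions less likely, and the article gives no sign that they are common.
- **Missed time is not a missed record.** With contraction over 60% of the record, every simulated record carried at least one flag. That helps little: under six of the seven smoothers every fully relaxed record carried one too, so a flag does not tell the two apart.
- **The percentages rest on an unstated filter.** This stands for their size. The cancellation of the baseline and the ceilings hold under any filter.
- **The text may misdescribe the cited algorithm or the software function.** This cannot be checked from the article. The rule as printed would then still need correcting. If the whole waveform meant a resting recording only, the missed contraction would fall away but the false flagging of rest would remain.

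A reader might also infer that the rule lowers the measured maximal displacement, above all near end range with the knee extended. That would require flagged segments to be cut and flags to cluster there. The article does not state the unit of exclusion, stationary resting noise has no such pattern, and no displacement bias was computed.

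**Conclusion.** The point holds for the offline exclusion step. As printed, the resting baseline is computed but cannot affect the result, and the threshold moves with the recording it is meant to judge. This follows from the text alone.

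The practical size depends on the smoothing. Heavier smoothing (2–10 Hz) discards about 16–50% of a relaxed record. Light smoothing (50 Hz) spares rest but marks almost none of a contraction that fills 90% of the record. These figures assume noise-like resting EMG and a 5-fold contraction; weaker contractions are not covered. Any effect on the knee-position comparison remains open, because it depends on the unit excluded and on how flags fall in the two positions.

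**What to change.** - **Threshold:** count activity when the normalised signal exceeds 3 (resting mean + 3 SD) for at least 0.1 s.
- **Baseline:** take the resting mean and SD from a longer quiet window, for example 5 s instead of 0.25 s.
- **Smoothing:** fix the low-pass cut-off in advance at a value where this rule rarely flags rest. In simulation 10 Hz or higher with a 5 s baseline gave about 0% false flags.
- **Unit:** exclude the whole repetition, not a segment of it, and average the remaining repetitions.
- **Reporting:** give the number of excluded repetitions by knee position.
- **Text:** if the software function works differently from the description, correct the description to match it and confirm that its threshold comes from rest.

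The cost is a few seconds of extra resting recording and a revised processing rule. Whether the software allows the threshold to be changed directly cannot be seen from the article. The value of 3 SD is a convention, so a sensitivity run at 2 SD should be added. Dropping whole repetitions can leave fewer than three in some means, which is a further reason to report the counts.
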